## Abstract

**Background:**

Despite great improvement in child oral health, some children subgroups still suffer from higher levels of dental caries. Geographic and socioeconomic barriers and the lack of access to dental care services are among common reasons for poor oral health in children. Historically in Australia, oral health therapists or dental therapists have been responsible for providing dental care for school children through the School Dental Services (SDS). The current SDS has been unable to provide sustainable dental care to all school children due to a reduction in workforce participation and limited resources. We propose a paradigm shift in the current service through the introduction of user-friendly technology to provide a foundation for sustainable dental care for school children.

**Methods/design:**

We describe an ongoing parallel, two-armed, non-inferiority randomised controlled trial that compares routine and teledental pathway of dental care in children aged 4–15 years (*n* = 250). Participating schools in Western Australia will be randomly assigned to the control or teledental group, approximately three schools in each group with a maximum of 45 children in each school. All participants will first receive a standard dental examination to identify those who require urgent referrals and then their teeth will be photographed using a smartphone camera. At the baseline, children in the control group will receive screening results and advice on the pathway of dental care based on the visual dental screening while children in the teledental group will receive screening results based on the assessment of dental images. At 9 months follow-up, all participants will undergo a final visual dental screening. The primary outcomes include decay experience and proportion of children become caries active. The secondary outcomes include the diagnostic performance of photographic dental assessment and costs comparison of two pathways of dental care.

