#### Visual dental examination

A standard dental screening (without radiography) will be performed by registered OHTs (operators) who are blinded to the group allocation of the school. Head-mounted lighting, disposable mirrors and probes will be used to conduct the visual dental screening. Findings from the visual dental assessment will be recorded on an oral health assessment form that follows the guidelines for oral health surveys developed by the WHO [35]. Following the completion of the baseline dental screening, parents of school children allocated to the control group will receive a copy of the screening results based on the visual inspection performed by onsite OHTs. Based on the severity and urgency of dental conditions, children with active caries will be referred to local dental providers for further investigations. Children who are screened caries-free or at low-risk, will not receive active treatment other than OHP leaflets.

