### Outcome assessment

*Primary outcomes* include decay experience in either dentition as measured by the DFT/dft (decay, filled teeth) index at the baseline and 9-month follow up. Teeth will be classified as carious if have arrested caries, caries into dentine or enamel level caries. In addition to the proportion of children becomes caries-active at the 9-month follow-up which refers to the percentage of children developing one or more new caries in any of the previously caries-free teeth when assessed at the baseline. Data will be collected from one of our system’s functional components running on the backend to automatically record dental assessments based on dental images and through the oral health assessment forms completed by OHTs in the control group.

*Secondary outcomes* include the diagnostic performance of photographic dental assessment versus standard dental examination at the baseline. The participants’ dental care utilisation patterns collected via a baseline survey (Additional file 2) and adapted from Kopycka-Kedzierawski et al. [36]. Also, costs comparison between the two pathways of dental care will be conducted to identify the least costly alternative. The resources for the usual pathway of dental care will include vehicle costs, admin costs (e.g. telephone appointments, printing services and postage) and costs of consumables used in visual dental screening and the dental practitioner’s time. The resources for the teledental pathway of dental care include: software licence fees, ICT equipment, Internet and software engineer’s time, admin costs (e.g. telephone appointments, printing services and postage), costs of consumables used in dental photography, tele-assistants (photographer) time, and offsite dental practitioners’ time for reviewing dental images. Dental care costs for all children include the following: restorations, restorations with crowns and extractions. The costing data will be based on those incurred by the health system and will be derived from a survey and web-based open-access sources [37].

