### Data analysis

The sensitivity and specificity values for the photographic caries assessment will be estimated and compared to the reference visual dental assessment at the baseline. Kappa statistic will be used to estimate the inter-rater reliability of the photographic dental assessments by two independent OHTs. 15% of dental images will be re-examined to test intra-rater reliability at least, 4 weeks after the initial review of images.

The baseline data will be used to generate descriptive statistics for the intervention and control groups (teledental versus usual care pathway). General linear regression models will be performed to compare the efficacy of the interventions on decay (mean DFT/dft) between intervention and control groups, adjusting for baseline data collected via a survey that includes tooth brushing (yes/no; frequency); dental visit patterns over the past year, child age, Indigenous status, Socio-Economic Indexes for Areas (SEIFA), private insurance status and educational level of parents. The measure of intervention efficacy will be the difference between the intervention and control groups in adjusted DFT/dft (caries incidence) per child. All analyses will be performed using SAS (version 9.4). In addition, a cost minimisation analysis will be undertaken to compare the costs associated with teledental versus the usual pathway of dental care over 9 months. This will include both the cost of the initial screening, and any subsequent interventions occurring over the 9 months. The analysis will be conducted from the perspective of the health system and, will not take into consideration the costs incurred by the families. All salaries used in the calculation will be based on Australian government rates and will include on-costs.

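### Every teledental child first has a visual triage examination, but its cost is charged only to usual care and the efficacy comparison makes no provision for it

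*Protocol article*

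**What the plan says.** The abstract (Methods/design) describes the baseline visit for both arms: "All participants will first receive a standard dental examination to identify those who require urgent referrals". The photographs are taken after that. What differs is the source of the advice that parents receive. The same paragraph says that "children in the teledental group will receive screening results based on the assessment of dental images", and the section Visual dental examination says that "parents of school children allocated to the control group will receive a copy of the screening results based on the visual inspection".

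For efficacy, the Data analysis section states: "The measure of intervention efficacy will be the difference between the intervention and control groups in adjusted DFT/dft (caries incidence) per child". It gives no exclusion, separate reporting or sensitivity analysis for children picked up by the visual triage.

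For cost, the Outcome assessment section charges the usual pathway with vehicles, administration, visual-screening consumables and the dental practitioner's time. On the other side, "The resources for the teledental pathway of dental care include: software licence fees, ICT equipment". That list goes on to internet and engineer time, administration, photography consumables and photographer time, and ends with "offsite dental practitioners’ time for reviewing dental images". Restorations, crowns and extractions are costed in both arms, and the cost-minimisation analysis runs from the initial screening through later care up to 9 months.

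The Objectives section hypothesises that the teledental pathway is as effective as usual care and saves cost. The design is non-inferiority.

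**The concern.** Three statements in the article do not describe the same intervention. The abstract gives the teledental arm a visual examination with a care purpose. The cost list prices a pathway without it. The efficacy comparison takes the arms as randomised, so it includes whatever the triage set in motion.

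A cost-minimisation analysis is sound only if the pathway that is costed is the pathway whose outcomes were found comparable. Here the outcomes come from triage plus photographs and the screening cost from photographs alone.

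In a non-inferiority trial, a step that makes detection identical in both arms for some children can only draw the arms together. The children concerned are those in whom a missed diagnosis matters most. A reader deciding whether photographs can replace an on-site examination would be relying on a comparison that did not fully test this.

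**Working it through.** **1. The two pathways side by side.**

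| Element | Usual care | Teledental |
|---|---|---|
| Visual examination to find urgent cases | Yes | Yes (abstract) |
| Source of routine results and advice | Visual examination | Images |
| Visual-screening consumables costed | Yes | Not listed |
| On-site dental practitioner time costed | Yes | Not listed; offsite image review only |
| Later dental care over 9 months costed | Yes | Yes |

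The examination is delivered in both columns and costed in one.

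**2. Direction for cost.** Compared with the pathway as delivered, the teledental cost is too low by the cost of the visual examination. That cost cannot be negative, so the omission favours a saving. Compared with a photograph-only pathway, the examination is rightly left out, but care that only the triage triggered is then wrongly left in. The costing matches neither pathway.

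**3. The plan's own figures.** Sample size calculation: n = 1.96² × 0.90 × 0.10 / 0.1² = 34.57, rounded up to 35 children with caries. At 35% prevalence, 35 × 0.65/0.35 = 65 without caries. The sum is 100, and 100/0.8 = 125 per group, as stated. This figure does not depend on the present point.

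**4. Direction for detection.** Let C be the caries cases in an arm, u the share of them found as urgent by the visual examination, and Se the child-level sensitivity of the images. The documents do not give u. Se is also assumed, once as 0.90 (the expected proportion in the sample-size section, read as sensitivity) and once as 0.70.

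- C = 125 × 0.35 = 43.75.
- Missed by photographs alone: C × (1 − Se).
- Missed with visual triage added: C × (1 − u) × (1 − Se).

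| Se (assumed) | Photographs alone | u = 10% | u = 30% | u = 50% |
|---|---|---|---|---|
| 0.90 | 4.4 | 3.9 | 3.1 | 2.2 |
| 0.70 | 13.1 | 11.8 | 9.2 | 6.6 |

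The shortfall shrinks by the proportion u, but only if Se is the same in urgent and other disease. With separate sensitivities Se_u and Se_n, the fraction of the shortfall removed is u(1 − Se_u) / [u(1 − Se_u) + (1 − u)(1 − Se_n)]. This equals u when the two are equal and falls to zero if images find every urgent case. The direction is fixed; the size is not.

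**5. From detection to the primary outcomes.** The table in step 4 counts detected children, not outcome differences. DFT/dft adds decayed and filled teeth, so a decayed tooth that is found and filled still counts as one. The caries-active outcome counts only teeth that were caries-free at baseline, so existing decay cannot enter it. Two routes remain by which triage can move the outcomes: extraction, which takes a tooth out of an index with no missing component, and indirect effects of treatment and advice on new lesions. The documents quantify neither.

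**The case against.** The strongest reply is that the visual examination is the reference standard for the diagnostic-accuracy objective and must be done in every child. Leaving a research test out of a pathway's cost is normal. This would settle the cost point if the result were used for research only. The abstract instead gives the examination the purpose of urgent referral, and the article states no rule that separates its care effects from its research use. The reply stands only in part.

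Second, the triage step appears in the abstract but is not repeated under The intervention, Visual dental examination or Photographic dental assessment. The article does not say outright that teledental children found urgent were referred on the visual result and kept in the analysis, the flow diagrams are not shown, and the full protocol may say more. This is a real limit, and it is why the point rests on the plain reading. The statement that the visual examiners are blinded to the school's group fits examination of both arms.

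Third, a reader might infer a large dilution from the urgent children's share of all decay. If 5% to 15% were urgent with 5 decayed teeth each, against a mean of 1.05 per child (35% × 3), the share would be 0.05 × 5/1.05 = 24% to 0.15 × 5/1.05 = 71%. The documents do not support this. The urgent fraction and both tooth counts are assumed, and existing decay that is filled changes neither primary outcome.

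Fourth, sensitivity and specificity at baseline are already planned, and extra sensitivity analyses often sit in an analysis plan. Those accuracy measures concern caries, not urgent referral, and the mismatch between pathway and cost list is in what the article itself states.

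**Conclusion.** The point holds as one of direction. On the plain reading of the abstract, the teledental arm receives visual triage before photography, the cost of that examination is charged only to usual care, and the efficacy comparison does not account for it. Both effects lean toward the trial's hypotheses: non-inferiority, because detection is made alike in urgent children, and cost saving, because an element that was delivered is not priced.

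The size cannot be computed from the documents. It depends on the urgent fraction, on how well images find urgent disease, and on routes to the outcome other than filling. The effect on the efficacy estimate could be small.

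A reader might also infer that the plan defines the teledental arm as photograph-only for efficacy. It does not: the Data analysis section compares the randomised groups. The weakness is that the resulting contrast does not isolate photographs. The diagnostic-accuracy objective is unaffected, since it needs both assessments in every child.

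**What to change.** Leave the urgent-referral procedure as it is and change the analysis and the claim. Data collection was still under way when the article was written, so these steps could be fixed in advance.

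1. In the teledental arm, cross-tabulate urgent referral on the visual examination against referral on image charting, and report the number missed by images.
2. Add a sensitivity analysis of both primary outcomes that excludes visually urgent children from both arms. The criterion comes from the same baseline examination in each arm, so the exclusion treats them alike.
3. Add a cost scenario that either charges the visual examination to the teledental arm, or excludes both the examination and the care it triggered.
4. Limit the efficacy and cost-saving conclusion to photographs plus visual triage unless the results hold in steps 2 and 3.

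The cost is a few additional analyses and perhaps a narrower claim. Both assessments are recorded for every child on forms that follow the same WHO guidance, but the article does not say whether either form holds an urgency field; this should be checked first. Estimates for urgent children will be imprecise: if 5% to 15% were urgent (assumed), that is 125 × 0.05 to 125 × 0.15, about 6 to 19 children per arm.

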**Discussion:**

The current project seeks to take advantage of mobile technology to acquire dental images from a child’s mouth at school settings and forwarding images electronically to an offsite dental practitioner to assess and prepare dental recommendations remotely. Such an approach will help to prioritise high-risk children and provide them with a quick treatment pathway and avoid unnecessary referrals or travel.

**Trial registration:**

Australian New Zealand Clinical Trials Registry, ACTRN12619001233112. Registered 06 September 2019.

## Background

Dental caries (tooth decay) remains the most prevalent chronic disease of childhood, even ahead of asthma and hay fever [1]. According to the Child Dental Health Survey 2010, the proportion of Australian children with caries experience (decayed, missing and filled teeth ‘dmft + DMFT’ > 0) varied from 48% for children aged 5 years to 69% for children aged 9 years [2]. There is a significant social gradient between socioeconomic status and the prevalence and severity of oral diseases which highlights oral health inequalities and inadequate funding for prevention and treatment [3]. Dental caries is an entirely preventable dynamic disease, with an interplay of risk factors that protect against or cause progression of the disease. In general diet, oral hygiene and fluoride exposure are the most common factors assessed when determining an individual’s risk level for the disease [4].

If dental caries remains untreated, it can have serious consequences that require costly treatment. Dental caries can lead to physical and psychosocial consequences including pain, sepsis, and disturbed eating, drinking and sleep pattern [3]. Poor oral health can have a significant impact on a child’s development including below average height, weight, and head circumference, and absenteeism from school [5, 6]. The demand for dental care is increasing and with it the total costs. Recurrent expenditure on dental care services in Australia increased from $6.6 billion AUD in 2006–07 to $10.2 billion AUD in 2016–17 (adjusted for inflation), at an average annual growth rate of 4.4% [7]. Dental extractions and restorations are the most common reported causes for hospital admission among Australian children [8]. For instance, between 2000 and 2009, a total of 43,937 children (0–14 years) were hospitalised due to various oral conditions in Western Australia (WA) with total costs of $92 million AUD [9].

Dental therapists or more recently oral health therapists (OHTs) have been responsible for providing most of the dental services (including examinations, fillings, extractions and preventive care) for school children ages 5–14 years through the government-funded school dental services (SDS) [10]. The history of SDS in Australia can be traced back to the 1920s, where it was designed to provide dental care for poor and disadvantaged children. Following the introduction of the Australian School Dental Scheme (ASDS) in 1973 [11], the SDS has expanded to cover all primary schools in all states and territories. Similar services are provided in several countries such as New Zealand, Canada, Hong Kong, Singapore and Malaysia [12]. Despite improvements in child oral health, nearly half the school children receiving dental care within the SDS do not enjoy good oral health [13]. In recent years, the SDS has suffered a reduction in workforce participation, scarcity of resources, and services remain largely concentrated in the metropolitan regions [14]. Until the 2000s, the employment of dental therapists was limited to the state-operated SDS [15]. Recently, many dental therapists have opted for private practice career or even leaving the profession which resulted in decreased retention and recruitment of dental therapists or OHTs in the SDS [16]. Therefore, the current SDS rarely provides sustainable dental care and is unable to meet all child oral health needs [13].

Children are at high risk of developing dental caries, but its impact can be reduced or prevented through early detection, early intervention, including caries risk assessment and tailored oral hygiene interventions and the provision of preventive dental care, particularly, in the early life [17, 18]. Therefore, it is important to regularly monitor the oral health of high-risk children to address the risk factors which can reduce the overall burden of the disease in the future [19]. However, reaching out to all school children, particularly, in rural regions, is challenging and costly. Thus, there is a need for an equitable and cost-efficient model of dental care to enhance the opportunity to provide sustainable dental care for school children, particularly those living in remote regions.

One of the potentially viable alternatives to address child oral health inequities and inequalities is the use of telehealth. Teledentistry is a form of telehealth that is specifically dedicated to dentistry and uses electronic medical records, information and communication technology (ICT), digital photography and the Internet for consultation, supervision or continuing education [20]. Telehealth, particularly, mobile technology, is an attractive innovation due to mobile connectivity, improving digital photography capabilities and the computational power of smartphones which allow their users to perform multiple tasks such as data processing, storage and transfer as well as access to low-cost, secure cloud storage. The use of a smartphone camera in dental photography can be useful for recording a baseline of oral health status pre-operatively, which can be used to confirm the diagnosis and preparing an appropriate treatment plan. As smartphones are widely carried and can be used at any time, they can be used as point-of-care devices to improve the delivery of patient-centred care. A telehealth model of care delivery suits role substitution in dentistry, particularly, facilitating data collection, health promotion and screening. At the screening level, trained teachers or school staff, using a user-friendly mobile technology, can help in collecting digital data from school children for later evaluation by a dental expert from a distance. Ample evidence indicated that the involvement of trained non-dental health personnel in the screening and provision of oral health promotion has been beneficial [21–23]. The use of telehealth can be ideal for the rural population who have no or limited access to health services [24].

The proposed project builds on previous validation trials that examined the feasibility of the teledentistry approach to dental screening [25–27]. The findings showed that the use of dental photography in dental screening is feasible and offered a moderate diagnostic accuracy relative to visual dental screening. Recent systematic reviews indicated that most reviewed studies concerned with teledental diagnosis demonstrated comparable results between photographic and visual inspection techniques [28, 29]. Although telehealth applications are becoming increasingly popular in dentistry, controlled assessments of clinical outcomes, long-term use and economic analyses of teledentistry are still limited [30–32]. A comparison of the costs of teledentistry and its alternatives is of great importance to those making future decisions about implementing a new service. In this study, we propose a paradigm shift in the existing dental services through role substitution and taking advantage of user-friendly mobile technology and the widely available Internet to improve school children access to dental services.

